### Unsolicited Adverse Events

A CRF will be provided to record unsolicited AEs. Unsolicited AEs are signs or symptoms reported by the subjects or their parents within 30 days of a vaccination that are different from those solicited symptoms recorded during the seven-day post-vaccination follow‑up period. Signs and symptoms that would fit the solicited AE category, but actually start after the sixth day post-vaccination, will also be considered unsolicited AEs. An investigator will ensure that any general (systemic) signs or symptoms reported will be evaluated, and their relationship with the study vaccine determined and transcribed onto the CRF.

## Assessment of Intensity

Intensity of solicited AEs will be assessed and graded by an investigator or clinician as presented in Exhibit 12.

| Exhibit 12. Assessment of Solicited Adverse Event (AE) Intensity | | |
| --- | --- | --- |
| **AE** | **Grade** | **Intensity Definition** |
| Pain at injection site | 0 | Absent |
|  | 1 | Minor reaction to touch |
|  | 2 | Cries/protests on touch |
|  | 3 | Cries when limb is moved or spontaneously painful or limping or reluctance to bear weight |
| Swelling at injection site | 0 | Absent |
|  | 1 | < 5 mm |
|  | 2 | 5-20 mm |
|  | 3 | > 20 mm |
| Fever | 0 | < 37.5°C |
|  | 1 | 37.5-38.0°C |
|  | 2 | 38.1-39.0°C |
|  | 3 | > 39.0°C |
| Irritability/Fussiness | 0 | Behavior as usual |
|  | 1 | Crying more than usual/no effect on normal activity |
|  | 2 | Crying more than usual/ interferes with normal activity |
|  | 3 | Crying that cannot be comforted/ prevents normal activity |
| Drowsiness | 0 | Behavior as usual |
|  | 1 | Drowsiness easily tolerated |
|  | 2 | Drowsiness that interferes with normal activity |
|  | 3 | Drowsiness that prevents normal activity |
| Loss of appetite | 0 | Normal |
|  | 1 | Eating less than usual/no effect on normal activity |
|  | 2 | Eating less than usual/interferes with normal activity |
|  | 3 | Not eating at all |

For all other AEs, maximum intensity should be assigned to one of the following categories:

0 = No adverse event

1 = An adverse event that is easily tolerated by the subject, causing minimal discomfort and not interfering with everyday activities.

2 = An adverse event that is sufficiently discomforting to interfere with normal everyday activities.

3 = An adverse event that prevents normal, everyday activities. (Such an adverse event would, for example, prevent attendance at school, church or other typical assemblies, and would necessitate the administration of corrective therapy.)

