## Safety Plan

### Criteria for Temporary Suspension of Vaccination

If any of the following SAEs occurs, the PI will ensure the temporary suspension of vaccination for all study subjects, and the events will be reported as described in Section 10.5 and in SSP No. MAL036-14.

1) Death in any subject where the cause of death is judged to be related to study vaccine

2) The occurrence in any subject of an anaphylactic reaction to study vaccine

3) The occurrence in any subject of a life-threatening SAE which is judged to be causally related to the vaccine (see definition of “Yes” as regards causality in Section 10.3, pg. 77)

4) The occurrence of a non-life-threatening SAE which is judged to be causally related to the vaccine

5) The occurrence, in one or more subjects, of laboratory abnormalities judged by the PI to be potentially life-threatening and related to receipt of study vaccine

The following findings will mandate temporary suspension of additional doses:

1. In 20 (5%) or more children, occurrence of Grade 3 solicited systemic (not local) AEs judged related to the study vaccine, or
2. In 20 (5%) or more children occurrence of Grade 3 unsolicited AEs judged related to the study vaccine.

NB: a) and b) will come from pooled, blinded data.

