### Dose Discontinuation in Individual Subjects

Reasons for discontinuation of study vaccine administration in an individual subject include, but are not limited to, the following:

1. Anaphylactic reaction following administration of study vaccine
2. Significant reactions (e.g., Grade 3 AEs) following administration of study vaccine (including severe pain, severe swelling, severe headache, persistent high fever or other severe systemic or local reactions) that, in the opinion of the investigator or sponsor, should preclude further administration of study vaccine
3. The occurrence of an SAE (See Section 10.5.1) related to the study vaccine
4. Receipt of any investigative drug, investigative vaccine or immunosuppressive medication (inhaled or topical corticosteroids are allowed) within 28 days of study vaccine
5. The occurrence of other medical conditions, unrelated to study vaccine that in the opinion of the PI contraindicate administration of study vaccine
6. Moderate or severe unsolicited AEs (clinical events or laboratory tests) that are indicative of new and significant end organ dysfunction and that, in the opinion of the investigator or sponsor, should preclude further administration of study vaccine

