## Eliciting and Documenting Adverse Events

### Definition of an Adverse Event

Reportable non-serious adverse events (RNAEs) are discussed in Section 10.1.4; serious adverse events (SAEs) are discussed in Section 10.5.

An adverse event (AE) includes any noxious, pathological, or unintended change in anatomical, physiological, or metabolic functions as indicated by physical signs, symptoms, or laboratory test abnormalities occurring in any phase of the clinical study whether associated with the study vaccine and whether considered vaccine-related. This includes an exacerbation of pre-existing conditions or events, intercurrent illnesses, a vaccine or drug interaction, or the significant worsening of a previously documented condition. A symptom present just prior to a first vaccination, and not exacerbated after the vaccination is administered, should not be considered an AE. Similarly, anticipated day-to-day fluctuations of pre-existing conditions,including the disease under study, that do not represent clinically significant exacerbations need not be considered AEs. However, discrete episodes of chronic conditions occurring during a study period (after the first vaccination) should be reported as AEs in order to assess changes in frequency or severity.

AEs should be documented in terms of a medical diagnosis. When this is not possible, an AE will be documented in terms of signs and symptoms observed by the investigator or reported by the participant at each study visit.

Pre-existing conditions, or signs and symptoms (including any that are not recognized at study entry but are recognized during the study period) that are present in a subject prior to the start of the study, should be recorded on the Medical History CRF. Any solicited sign or symptom present during a pre-vaccination assessment should be recorded on the Pre‑Vaccination Assessment CRF.

AEs that occur after informed consent is obtained, but prior to a first vaccination, will be documented on the Medical History CRF.

Any non-elective hospitalization will be considered an SAE, rather than an AE, regardless of the reason for hospitalization and possible causal relationship to vaccine administration (See Section 10.3).

Solicited AEs to be recorded are described in Section 10.1.5. Any other AEs will be recorded as unsolicited AEs.

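### A symptomless laboratory abnormality is always Grade 1 under Section 10.2, so it cannot enter the pooled Grade 3 count in 6.9.1 and does not fit the wording of 6.9.6(6)

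*Protocol*

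**What the plan says.** Protocol Section 10.1.1 defines an adverse event to include "physical signs, symptoms, or laboratory test abnormalities occurring in any phase of the clinical study". After pointing to the solicited list, it adds: "Any other AEs will be recorded as unsolicited AEs". A laboratory AE is therefore an unsolicited AE.

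Section 10.2 grades the six solicited symptoms in Exhibit 12. It then says: "For all other AEs, maximum intensity should be assigned to one of the following categories". Apart from 0 for no event, the categories are:

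- Grade 1: "An adverse event that is easily tolerated by the subject, causing minimal discomfort and not interfering with everyday activities".
- Grade 2: "An adverse event that is sufficiently discomforting to interfere with normal everyday activities".
- Grade 3: "An adverse event that prevents normal, everyday activities".

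Two provisions on dosing depend on intensity. Section 6.9.1 suspends vaccination when 20 or more children (5%) have "occurrence of Grade 3 unsolicited AEs judged related to the study vaccine", counted on pooled, blinded data. Section 6.9.6, item 6, lists as a reason to stop dosing in one child: "Moderate or severe unsolicited AEs (clinical events or laboratory tests) that are indicative of new and significant end organ dysfunction", where the investigator or sponsor considers that this should preclude further vaccine.

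**The concern.** The trial draws blood for ALT, creatinine and blood counts to find changes that a child aged 12 to 47 months may not show outwardly. The scale for these findings asks only whether the child is uncomfortable or kept from usual activity. Followed literally, it gives the lowest grade to any silent abnormality, large or small.

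Two things are at stake. The pooled Grade 3 count cannot register silent laboratory events. And item 6 of 6.9.6 names laboratory tests at an intensity for which Section 10.2 offers no route without symptoms, so two investigators could reasonably read it in different ways.

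**Working it through.** **1. The plan's own figure.** 400 children are randomized (Section 6.1) and the 6.9.1 threshold is 20 children: 20/400 = 0.05. The stated 5% is right.

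**2. The scale applied literally.** Take a laboratory abnormality without symptoms.

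- Is it an AE? Yes (10.1.1).
- Which class? Unsolicited, because it is not among the solicited symptoms (10.1.1).
- Which scale? The general one, because Exhibit 12 contains no laboratory test (10.2).
- Which grade? It does not interfere with activity, so it is neither Grade 2 nor Grade 3. The highest grade available is 1, and the measured value plays no part.

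In the same section, Exhibit 12 grades fever by temperature and swelling by diameter, so grading by measurement is already the protocol's practice.

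**3. Effect on the pooled count.** Let k be the number of children with a silent, related laboratory AE. Their contribution to the Grade 3 count is 0 for k = 1, 20, 100 or 400, and 0 < 20 in each case.

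For scale only, suppose laboratory AEs did have value-based grades and these counted. With a true pooled rate p of related Grade 3 laboratory events, the chance of meeting the threshold is P(X ≥ 20) with X ~ Binomial(400, p):

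| Assumed p | P(X ≥ 20) |
| --- | --- |
| 2% | 0.0002 |
| 3% | 0.020 |
| 5% | 0.53 |
| 8% | 0.993 |
| 10% | 0.9999 |

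The protocol gives no such rate, so these values of p are assumptions. Under the present text the contribution is zero in every row.

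**4. Section 10.2 against 6.9.6(6).** Section 10.2 numbers its grades and uses neither the word moderate nor the word severe. If moderate means Grade 2 and severe means Grade 3, a silent laboratory AE cannot reach either. If the words are not tied to the scale, they are undefined for laboratory tests. The two sections do not fit on either reading.

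**5. How many draws are concerned.** CBC, creatinine and ALT are scheduled after the first dose at about Study Days 29, 57 and 85 (Section 8.1): at most 3 × 400 = 1,200 panels. This is an upper bound, for three reasons.

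- Day 85 follows the last dose, so it affects tabulation and not dosing.
- Day 57 blood is drawn just before dose 3, and Visit 12 reviews the day 29 results (Section 7.2). Mainly the day 29 panel, about 400 samples, can inform a later dose.
- Exhibit 7 shows no creatinine or ALT at Visit 17 (day 85), while Sections 7.2 and 8.1 include them. If Exhibit 7 governs, those two tests give at most 2 × 400 = 800 results after the first dose.

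**The case against.** The strongest answer is that little depends on the grade. Most of this stands, and it limits the point:

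- **Numeric limits are revisited.** The Section 6.5 limits for ALT, creatinine, hemoglobin, platelets and lymphocytes are looked at again before doses 2 and 3 and can defer vaccination. Visits 7 and 12 call for review of the criteria and of earlier laboratory results.
- **Other routes need no grade.** Section 6.9.1(5) covers related laboratory abnormalities that the PI judges potentially life-threatening. SAE reporting and the RNAE memorandum are available, and the 6.9.6 list is open-ended.
- **Laboratory data are analyzed directly.** Section 12.4.5 fits mixed models to CBC, creatinine and ALT, so the comparison by arm does not rest on AE grades.
- **The Section 6.9.2 report is not materially affected.** It covers seven days after each dose, and no safety bloods are scheduled in that window.
- **Section 10.1.6 describes unsolicited AEs as reported signs or symptoms.** One could argue that silent laboratory findings were never meant for the intensity table. But 10.1.1 and 6.9.6(6) say otherwise, so this adds to the inconsistency.

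A reader might infer that the suspension and discontinuation rules cannot operate at all, or that 6.9.1(5) is the only laboratory safeguard. The documents support neither. Clinical events and symptomatic laboratory abnormalities still count, and the safeguards above remain. However, none of those safeguards assigns a grade, adds to the pooled Grade 3 count or changes an intensity table.

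**Conclusion.** The point holds in this limited form. Under Section 10.2 a symptomless laboratory AE is Grade 1 at any value. Its contribution to the 20-child Grade 3 count in 6.9.1 is therefore zero at any frequency, and it appears as Grade 1 wherever AE intensity is tabulated. Section 6.9.6(6) presupposes a laboratory intensity that 10.2 does not provide.

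This is more than detail left to a later document, because the stated scale yields an uninformative grade and conflicts with another section. It is not evidence that children are unprotected or that laboratory effects would go unseen by arm.

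The conclusion assumes that 10.2 is applied as written and that no unseen procedure holds a laboratory grading table. Section 10.2 refers to none, and no title in Appendices B and C names one.

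**What to change.** In Section 10.2, take laboratory AEs out of the activity-based scale and grade them by measured value. Use one pediatric toxicity table for ALT, creatinine, hemoglobin, platelets and lymphocytes, chosen by the sponsor and DSMB against the site's reference ranges.

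Reconcile 10.2 with 6.9.1 and 6.9.6(6), so that the text says how laboratory grades relate to those provisions and what moderate and severe mean for a laboratory test. The cut-offs and the operation of the rules remain for the sponsor and DSMB. Align Section 10.1.6 with 10.1.1 on whether laboratory findings are unsolicited AEs, and settle whether creatinine and ALT are drawn at Visit 17.

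The cost is one table and matching CRF instructions. The grades can be derived from results already collected. The downside is a somewhat longer list of graded laboratory AEs.

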## Assessment of Causality

For each AE, the investigators will ensure that a determination is made on the presence or absence of a causal relationship to the administration of the study vaccine.

The degree of certainty with which an AE can be attributed to administration of the study vaccine (or alternative causes, e.g., natural history of underlying diseases, concurrent therapy, etc.) will be determined by how well the event can be understood in terms of one or more of the following:

- Reactions of a similar nature having previously been observed with this type of vaccine or formulation.
- The event having often been reported in literature for similar types of vaccines.
- The event being temporally associated with vaccination or reproduced on re-vaccination.

All fevers occurring within 24 hours of a vaccination will be considered causally related to the vaccination unless a plausible concurrent illness is a more likely cause. All solicited local (injection site) reactions that occur within 24 hours of vaccination will be considered causally related to vaccination.

Assessment of causality in all other AEs should be documented by the investigators or clinicians by answering the following query on the Serious and Unexpected Adverse Event Report:

“In your opinion, did the vaccine(s) possibly contribute to the adverse event?”

NO: Either the adverse event is not causally related to administration of the study vaccine, or there are other, more likely causes and administration of the study vaccine is not

suspected to have contributed to the adverse event.

YES: There is a reasonable possibility that the vaccine contributed to the adverse event.

Non-serious and serious AEs will be evaluated as two distinct events given their different medical nature. The PI will investigate an event that meets the criteria to be determined “serious” (see Section 10.5.1 for definition of an SAE), to the extent that a determination of ALL relevant contributing factors can be made.

A partial list of possible contributing factors might include:

- Past medical history
- Concurrent medications
- Protocol required procedures
- Lack of efficacy of the test vaccine
- Erroneous vaccine administration

## Adverse Event Follow-up and Assessment of Outcome

Investigators should follow up subjects with SAEs until the event has subsided, or until the condition has stabilized, regardless of when this occurs in relation to the study conclusion. Investigators should follow up subjects with non-serious AEs until study conclusion for a given subject.

Only one of the following outcomes should be documented:

1 = Recovered without sequelae

2 = Recovered with sequelae

3 = Worsened (New AE)

4 = Died

5 = Unknown

And, if ongoing at the subject’s study conclusion,

6.1 = Ongoing and unchanged

6.2 = Ongoing, but improved

6.3 = Ongoing and worsened

## Serious Adverse Events

### Definition of a Serious Adverse Event

A serious adverse event (SAE) is any untoward medical occurrence that results in death, is *life-threatening*, results in persistent or significant *disability or incapacity*, requires in-patient *hospitalization* or prolongation of existing hospitalization, or is a congenital anomaly or birth defect in the offspring of a study subject. In addition, important medical events that may require intervention to prevent one of the other outcomes listed above should be considered serious. (Examples of such interventions include intensive treatment in an emergency room, out-patient clinic or at home for allergic bronchospasm; blood dyscrasias or non-febrile seizures that do not result in hospitalization; and development of drug dependency or drug abuse.)

Additionally, the following will always be reported as SAEs: (1) any clinical management involving use of parenteral antimalarials and (2) any subjects meeting the definition of severe falciparum malaria according to the 2000 World Health Organization criteria (see Section 16.6; Appendix F).

Although not considered to be SAEs, elective hospitalizations, pregnancies and cancer diagnoses should be reported in the same expedited fashion as SAEs. No pregnancies are anticipated in this pediatric study. They are categorized as a special type of AE: the reportable, non-serious adverse event (RNAE) (See Section 10.1.4).

Definitions of terms used in the above definition of an SAE are:

*Life-threatening*: An adverse event is life-threatening if the subject was at risk of death at the time of the event; it does not refer to an event that hypothetically might have caused death if it were more severe.

*Disabling or incapacitating*: An adverse event is incapacitating or disabling if the event results in a substantial disruption of the subject's ability to carry out normal life functions. This definition is not intended to include experiences of relatively minor medical significance such as headache, nausea, vomiting, diarrhea, influenza, and accidental trauma (*e.g*., sprained ankle).

*Hospitalization*: In general, hospitalization signifies that the subject has been detained (usually involving at least an overnight stay) at the hospital or emergency ward for treatment that would not have been appropriate in the physician’s office or other out-patient setting.

*Routine clinical procedure*: A procedure which is defined in the protocol as one that may take place during the study period and should not interfere with the study vaccine administration or any of the ongoing protocol specific procedures.

If anything untoward is reported during an elective procedure, that occurrence must be reported as an AE, either ‘serious’ or ‘non-serious’, according to the usual criteria.

When in doubt as to whether ‘hospitalization’ occurred or was necessary, the event should be considered an SAE.

It is the intent to capture and document 100% of the SAEs through the mechanisms detailed in Section 7.3 and Section 16.3.3 (in Appendix D). A subject’s parents will be instructed to contact the investigator at any time should the subject manifest signs or symptoms that they perceive as serious. They will be reminded to report to the nearest field station in the event of illness, so that transportation to the WRP KC can be arranged. They will be counseled to seek medical attention only through the WRP KC.

### Reporting Serious Adverse Events

Unanticipated problems involving risk to subjects or others, serious adverse events related to participation in the study and all subject deaths will be promptly reported by [contact]), by email ([[contact]](mailto:[contact])) or by [contact]) to the Army Surgeon General’s Human Subjects Research Review Board (HSRRB). If not submitted with the initial notification, a complete written report will follow within 3 working days. In addition to the methods above, the complete report will be sent to the U.S. Army Medical Research and Materiel Command, ATTN: MCMR-ZB-QH, [name].

During the first eight and a half months of the study (through Study Day 240), all SAEs, *whether or not they are judged to be related to the test article or comparator vaccine*, will be reported as detailed above, as well as to GSK Biologicals. In addition, the following organizations will receive copies of the written report, and so will be notified within three working days: KEMRI ERC, MVI/PATH, SCI, LMM, the DSMB, USAID, and WRAIR ORM.

After Study Day 240, SAEs will be reported monthly for the remainder of the study. Exceptions to this are: 1) any death in a study subject or 2) any SAE thought to be vaccine-related. These SAEs will be reported within 24 hours, as stated in the first two paragraphs of this section. The following organizations will receive copies of the monthly SAE reports: KEMRI ERC, HSRRB, MVI/PATH, USAMMDA, GSK Biologicals, SCI, LMM, DSMB, USAID, and WRAIR ORM.

Every SAE that is not resolved at the time the initial written report is filed will have a follow-up report submitted when information is available. Any submitted report will be identified as “initial”, “follow-up”, or “medical monitor” report.

An initial notification will include:

- Name of the PI
- Study protocol number
- Subject ID number, initials, age, and gender
- Date of onset of the event
- Date of the most recent administration of the study vaccine

The PI will not wait to collect additional information to fully document the event before making notification of an SAE. The telephone or email report should be followed by a full written report utilizing the Serious Adverse Events CRF, detailing relevant aspects of the SAEs in question.

Instances of death, cancer, or congenital abnormality in offspring, if brought to the attention of the investigator AT ANY TIME after cessation of the study, AND suspected by the investigator to be related to study vaccine, should be reported to the study sponsor.

Copies of all documents relating to SAE reporting will also be sent promptly by the PI to the study sponsor (POC: [name], USAMRMC, [name], USA). It is the sponsor’s responsibility to submit all SAE reports to the FDA.

Points of contact for the above mentioned individuals, committees, and institutions are given below.

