### Vaccination Process

On each vaccination day, criteria for continued eligibility will be reviewed and reverified. A history-directed physical examination will be done and axillary temperature, pulse, blood pressure, respirations and baseline general symptom history will be recorded. Venous blood will be collected for laboratory analysis as detailed in Section 8.1.

After the identity of the subject is checked (by comparing the SID number and photograph in subject’s record with the parent/subject’s photo ID), subjects will be vaccinated by intramuscular injection into the left anterolateral thigh muscles unless a compelling reason for using the right anterolateral thigh is evident (See also SSP No. MAL036-04: Vaccination Day Procedures). All vaccinations will be done in a fashion that maintains double-blinding (See Section 9.5.1). The vaccination periods may be up to ten consecutive days, but every effort will be made to vaccinate all 400 children over seven days.

Although all the foregoing study days are provisional (circumstances may require delays of up to two weeks), vaccinations (200 test article recipients, 200 rabies vaccine recipients) will occur on or about Study Days 0 (Dose 1), 29 (Dose 2), and 57 (Dose 3).

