## The Local Medical Monitor (Local Safety Monitor)

The Local Medical Monitor (LMM) will be an experienced, host nation physician based near the study site. The LMM must have the experience required to monitor human subjects during the conduct of a clinical trial and must be prepared to provide care to research subjects if any such need arises during the conduct of the study. In addition to the LMM, an alternate LMM, possessing the same qualifications, will be designated before study start. This alternate LMM will assume all the LMM’s responsibilities if the latter cannot meet his or her obligations.

The overall role of the LMM will be to vouchsafe responsible actions with regard to the ethics and clinical safety of a study, especially in regard to the proper assessment of AEs. At the same time the LMM should support the clinical investigators and act as a facilitator between them and the DSMB.

The PI will report all SAEs to the LMM, who will review them and provide an unbiased written report of events within ten calendar days of the initial report. At a minimum, this report will comment on the outcomes of the SAE, relationship to the test article, and indicate concurrence or non-concurrence with the details of the report provided by the PI.

Reports from the PI to the LMM detailing all SAEs and Grade 3 AEs for the seven day (vaccination day and six subsequent days), post-dose observation period, will also be provided to the DSMB, MVI, GSK Biologicals, and SCI following the administration of the first and second doses. This report will be submitted no less than seven days before the upcoming dose. After reviewing each report, the LMM will, if she concurs, recommend proceeding with the next scheduled dose. This concurrence may be given informally (e.g., telephonically) but will be recorded by the PI in the study regulatory file.

The LMM’s involvement will be particularly important when decisions have to be made quickly. Code break envelopes will be in the safekeeping of the LMM, who may unblind individual study subjects if necessary for medical or ethical reasons. In exceptional circumstances (e.g., a death possibly related to vaccination) the LMM would have the authority to suspend the whole or any specific aspect of the trial. The LMM may then call for trial resumption after discussion with, and approval by, the DSMB.

The LMM’s role will include:

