### Role of the Board

The DSMB may convene at any time during the study to review relevant safety data and to review and approve the Reporting and Analysis Plan (RAP). Meetings must be documented and minutes made available for the study files on site and to the sponsor. The DSMB may, if deemed necessary, convene a meeting with, or request further information from, the PI, the LMM, and designated project representatives of the WRAIR, GSK Biologicals, and MVI /PATH at any stage of the study; unscheduled meetings may be required.

The main role of the DSMB is to review and analyze clinical safety data collected during the trial and to assess SAEs.

The PI must provide the DSMB with:

- Prompt reports of any SAEs occurring during the study.
- Copies of LMM reports of Grade 3 solicited AEs after doses 1 and 2
- Any protocol amendments, informed consent changes or revisions of other documents originally submitted for review.
- Any new information that may adversely affect the safety of the subjects or the conduct of the study.

The DSMB can put the study on hold pending review of potential safety issues (see Section 6.9.2). All SAEs, including death, will be reported by the PI to the LMM, DSMB, the Manager of Clinical Safety Vaccines at GSK Biologicals, the HSRRB, KEMRI/ERC and MVI/PATH. The DSMB will review all SAEs for data trends in relation to safety issues and will have the right to seek additional clinical data about all cases. The DSMB will seek the input of the PI as needed. The DSMB may perform any of its own statistical calculations deemed necessary to support recommendations to the sponsor. All documentation provided to Board members for information and review must be treated in a confidential manner.

MVI will propose new members for the committee in the event that members must be replaced.

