## Appendix D: Overview of Study Operational Scheme

### Operational Study Milestones

All dates are hypothetical and provisional and are intended for planning purposes only.

Begin recruiting: 6 Dec 2004

Begin screening: 10 Jan 2005

Dose 1: 7-11 Feb 2005 (about 57 subjects/day for 7 days)

Dose 2: 28 Feb – 4 Mar 2005 (about 57 subjects/day for 7 days)

Dose 3: 28 Mar – 1 Apr 2005 (about 57 subjects/day for 7 days)

Efficacy Follow-up Period: 11 Apr to 27 Sep 2005 (o/a SD 71 to SD 240)

Addendum Efficacy Follow-up Period: 27 Sep to 10 Feb 2006 (o/a SD 240 to SD 364)

Intention-to-treat Follow-up Period: 7 Feb 2005 to 10 Feb 2006 (SD 0 to SD 364)

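### For an SAE, above all a death, that the PI has not judged vaccine-related, Section 10.5.2 lets three working days pass before the local medical monitor and the DSMB need be told, and no other timed route reaches them sooner

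*Protocol*

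**What the plan says.** Protocol Section 10.5.2 has two tiers of SAE reporting up to Study Day (SD) 240. The first is a prompt initial notice to the HSRRB, extended to GSK Biologicals, for every SAE whether or not it is thought related. The second is a list of bodies that "will receive copies of the written report, and so will be notified within three working days: KEMRI ERC, MVI/PATH, SCI, LMM, the DSMB", together with two others. For the LMM and the DSMB, the written copy is therefore the notification that this section provides.

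Section 13.2 says of the LMM that his or her "involvement will be particularly important when decisions have to be made quickly". It adds that in exceptional circumstances, with a death possibly related to vaccination as the example, "the LMM would have the authority to suspend the whole or any specific aspect of the trial". Section 13.3.2 obliges the PI to give the DSMB "Prompt reports of any SAEs occurring during the study".

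A faster route exists for some events. Under Section 6.9.1 any SAE judged causally related (fatal, life-threatening or neither), any anaphylactic reaction to study vaccine, and certain related laboratory abnormalities oblige the PI to suspend all vaccination. Section 6.9.3 then requires an email within 24 hours to the LMM and the DSMB, among others.

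On pace, Section 7.1.2 states that "every effort will be made to vaccinate all 400 children over seven days" and also that "The vaccination periods may be up to ten consecutive days". Section 16.3.1 plans "about 57 subjects/day for 7 days" for each dose.

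**The concern.** The person with emergency authority to halt the trial sits on the slower list. The faster route depends on the PI's own causality call: suspension criteria 1, 3 and 4 in Section 6.9.1 each require that the event be judged related. Section 10.3 lets the answer be NO when other causes are more likely and the vaccine is not suspected. Section 4.1 describes a holoendemic site, so a competing explanation for a child's death or severe illness will often be at hand. A second reader of causality matters most for exactly these events, and for them the only deadline is three working days. Dosing within a round can go on meanwhile.

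**Working it through.** **Which routes reach the LMM and the DSMB, and how fast**

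| Section | Trigger | Recipient | Time stated |
| --- | --- | --- | --- |
| 10.5.2, initial notice | any SAE to SD 240 | HSRRB, GSK Biologicals | prompt, no hours given |
| 10.5.2, written copy | any SAE to SD 240 | LMM, DSMB, others | three working days |
| 6.9.3 | PI concludes that a 6.9.1 criterion is met | LMM, DSMB, sponsor, partners | 24 hours, dosing already stopped |
| 6.9.2 | seven-day report after each dose | LMM, copy to DSMB | at least seven days before doses 2 and 3 |
| 7.1.3 | clinician finds an SAE | LMM, DSMB, IRBs, sponsor | none; refers to 10.5.2 |
| 7.1.6 | SAE in the efficacy period, which starts at SD 71 | ORP | 24 hours if possible |
| 13.2 | any SAE | LMM | none for the PI's report |
| 13.3.2 | any SAE | DSMB | prompt, no hours given |

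Only Section 6.9.3 gives the LMM or the DSMB a deadline shorter than three working days, and it needs a criterion to be met first. Section 6.9.2 acts between rounds, so it does not protect children still to be dosed within a round. The 24-hour rule in Section 7.1.6 names neither body and, read literally, begins after the third dose.

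**How many children could be dosed first**

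Inputs: 400 children (Section 6.2); seven days or up to ten (Section 7.1.2); up to 25 enrollment days (Summary, Study Duration); a delay of three days (Section 10.5.2), taken as three consecutive dosing days.

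The plan's own rate reproduces: 400 / 7 = 57.1, stated as about 57 (57 × 7 = 399).

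Children dosed before notice = daily rate × days of delay; about half are in the test arm (1:1 randomization).

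- Seven-day pace: 57 × 3 = 171, or 171 / 400 = 43% of the trial; about 86 in the test arm.
- Ten-day pace: 400 / 10 = 40 per day; 40 × 3 = 120; about 60 in the test arm.
- 25 days: 400 / 25 = 16 per day; 16 × 3 = 48; about 24 in the test arm.
- SAE judged related: the PI stops dosing at once, so about 0.

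If the initial notice reached the LMM within 24 hours (an assumed interval, borrowed from Section 6.9.3, since Section 10.5.2 gives no hours for its initial notice), the figures would be 57, 40 and 16.

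The provisional dates in Section 16.3.1 span five calendar days per dose although the same lines say seven. At five days the rate would be 400 / 5 = 80 and three days would give 240. I do not rely on this, because the section calls its dates hypothetical.

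**A loose cross-reference**

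For the period after SD 240, Section 10.5.2 requires deaths and vaccine-related SAEs to be reported within 24 hours and attributes that limit to its own first two paragraphs. Those paragraphs speak only of prompt notice and three working days.

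**The case against.** The strongest reply is that most of what matters already travels fast. The causality question in Section 10.3 asks whether the vaccine possibly contributed, and YES needs only a reasonable possibility. A death that the PI regards as possibly related, which is the example in Section 13.2, therefore stops dosing and reaches the LMM and the DSMB within 24 hours. Section 10.5.2 also tells the PI not to wait for more information before notifying, and Section 13.2 has the LMM work closely with the PI. Three working days could then be only an outer limit for paper. Operational detail may sit in the study-specific procedures for SAE reporting and for suspension (MAL036-05 and MAL036-14), which are not shown. A tiered scheme, slower for unrelated events, is a defensible choice, and SAEs here include any non-elective hospitalization and any parenteral antimalarial treatment.

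Much of this stands, and it rules out stronger readings that a reader might infer:

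- That the LMM and the DSMB hear of every SAE only by written copy. Section 6.9.3 shows otherwise for related SAEs and anaphylaxis.
- That about 171 children would be dosed after an SAE in general. That figure needs an event not judged related, early in a round, with notice at the last permitted moment.
- That the figure could be 57 × 5 = 285. This assumes a weekend inside the three working days with dosing continuing through it. Consecutive-day dosing is allowed, but nothing says that it will fall that way.
- That the protocol sets the LMM up as independent. It uses that word for the DSMB; from the LMM it asks an unbiased report.

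The reply does not close the remaining gap. An event called NO, or not yet called, has no timed route other than the written copy. Close working relations and the word prompt are not deadlines, and the section that governs SAE reporting sets three working days.

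**Conclusion.** The point holds in a limited form. Up to SD 240, an SAE that the PI judges unrelated or has not yet judged may reach the LMM and the DSMB as late as three working days afterwards, while the HSRRB and GSK Biologicals are told first. This fits badly with the quick-decision and suspension role in Section 13.2 and with the prompt reports promised in Section 13.3.2. Deaths are the most important case.

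The size is a ceiling on what the text permits, not an expected number: 171 children at the seven-day pace, 120 at ten days, 48 over 25 days, both arms counted. It assumes an even daily rate, three consecutive dosing days and the latest permitted notice. The gap is narrow, but it concerns safety oversight during dosing and costs almost nothing to close.

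**What to change.** In Section 10.5.2, add the LMM and the DSMB to the initial telephone or email notification through SD 240, ideally for every SAE and at minimum for all deaths and life-threatening SAEs regardless of the PI's causality call. Keep three working days for the full written report. Reconcile Sections 6.9.3, 7.1.3, 13.2 and 13.3.2 with that list so that each gives the same recipients and times. Correct the reference in Section 10.5.2 to a 24-hour limit that its first two paragraphs do not state.

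The cost is a sentence or two of text, further addressees on a message that is already sent, and some more initial notices for the LMM and the DSMB to read; the minimum version keeps that number small. No dose, schedule or suspension criterion changes.
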